**
[figure not shown]
**

A key step in the pathogenesis of atherosclerosis is impaired endothelial function, and it is positively correlated with obesity (Brook, 2006). A chief function of vascular endothelium is to regulate vascular smooth muscle tone. Using flow-mediated dilation (FMD), brachial artery diameter responses can be measured and used to evaluate endothelial function (Korkmaz and Onalan, 2008). Abnormalities in arterial function contribute to an increased risk of cardiovascular events in obese patients (Ortega et al., 2016). Previous studies have established that obesity is positively correlated with arterial stiffness, which is a key characteristic of atherosclerosis (Van Guilder et al., 2006; Acree et al., 2007). Pulse wave velocity (PWV) is known as an indicator of arterial stiffness. Aortic arterial stiffness is measured by carotid-femoral PWV (cfPWV), and systemic arterial stiffness is measured by brachial-ankle PWV (baPWV). These markers are considered to be simple and reliable indicators of conditions of central and systemic arterial function.

- 1. **Obesity and endothelial progenitor cells (EPCs)**

Recent studies suggest that an injured endothelial monolayer is regenerated by circulating bone marrow derived-EPCs, and thus, circulating EPC levels reflect the endothelial repair capacity (Koutroumpi et al., 2012). An altered status of circulating EPCs indicates endothelial dysfunction, and thus, the level of circulating EPCs could be used as a surrogate index of cumulative cardiovascular risk (Koutroumpi et al., 2012). An altered status of circulating EPCs indicates endothelial dysfunction, and thus, the level of circulating EPCs could be used as a surrogate index of cumulative cardiovascular risk (Koutroumpi et al., 2012). In fact, in 2008, Muller-Ehmsen et al. demonstrated for the first time that obesity is associated with a decreased number of circulating progenitor cells (Muller-Ehmsen et al., 2008). Further studies revealed evidence to support that there is a reduction in the number and function of EPCs in obese subjects (MacEneaney et al., 2009; Heida et al., 2010; Tobler et al., 2010).

- 1. **Effects of exercise on cardiovascular function**

Physical inactivity is one of the main risk factors for the development of several chronic degenerative diseases such as cardiovascular disease, diabetes, osteoporosis and some types of cancer. Active lifestyle is associated with less body fat, improved cardiovascular, bone and muscle function, reduced anxiety and depression (Weinsier et al., 1998).

Previous studies recognize that an improvement in endothelial function occurs in obese people by exercise (Sawyer et al., 2016) and diet intervention (Sasaki et al., 2002), and that combining both exercise and diet induces the most significant improvements (Woo et al., 2004).

Thereafter, research was done on the effect of physical activity on EPC mobilization, and it produced some interesting findings. For example, physical exercise had a positive effect on EPC mobilization by increasing both the number of EPCs and their functions (Van Craenenbroeck et al., 2010; Schlager et al., 2011; Cesari et al., 2012). However, the underlying mechanisms have not been elucidated.

1. **Objective**

To investigate the effects of an 8-week intervention program of a combination of exercise and diet on cardiovascular function including endothelial function, the number and functions of EPCs, autonomic function and arterial stiffness in obese adults, and the underlying mechanisms.

1. **Method**
   1. **Study design**

**Participants**

Obese adults from a traditional weight loss camp will be recruited to this study. The closed weight loss camp has uniformly managed accommodations, a controlled diet, and required physical training during the 8-week intervention period. The campers will be housed in the same building and could not move in and out freely during their stay. The measurements will be conducted before and after the subjects completed this 8-week weight loss program of exercise and diet.

Informed consent will be obtained from each individual prior to the measurements. This study will be conducted according to the Declaration of Helsinki. And the study will obtain approval from the Ethics Committee of Guangzhou Sport University.

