**Exclusion criteria**

Unstable angina pectoris, myocardial infarction within the last 12 months, decompensated heart failure, cardiomyopathy, severe valvular heart disease, considerable pulmonary disease, uncontrolled hypertension, kidney failure, orthopaedic and/or neurological limitations to exercise, surgery during the intervention period, and drug or alcohol abuse.

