**Primary and secondary outcomes**

Primary outcome is endothelial function which is assessed by FMD. Secondary outcomes include anthropometry, resting heart rate, blood pressure, body composition, aerobic fitness, maximal strength, EPC number and function, arterial stiffness (cfPWV, baPWV, central blood pressure, and augmentation index (AIx)), cardiac autonomic function (standard deviation of normal-to-normal intervals (SDNN), square root of the mean squared differences of successive normal-to-normal intervals (RMSSD), total power (TF), low-frequency power in normalized units (LFnu), high-frequency power in normalized units (HFnu), and low-frequency power/high-frequency power (LF/HF)), and multiple biochemical markers (lipid profiles, insulin, tumor necrosis factor-alpha, high-sensitivity C-reactive protein, superoxide dismutase, vascular endothelial growth factor, endothelial nitric oxide synthase, adiponectin and irisin).

- 1. **Sample size**

Sample size is calculated based on 1% change in FMD after weight loss with an expected standard deviation in FMD from our laboratory of 1.3%. The sample size required for the study, with an α of 0.05 and β of 0.20 at 5% level of significance (two-sided) and estimating a refusal rate of 20%, is 20 subjects.

- 1. **Measurement procedures**

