**EPC adhesion assay**

For the EPC adhesion assay, EPCs will be isolated and resuspended in M199 medium with 5% FBS. An equivalent amount of cells will be placed on a fibronectin-coated 96-well plate and incubated at 37˚C in 5% CO_2_ for 6 hours. After two gentle washes with PBS, adherent cells will be counted by independent, blinded investigators.

- 1. **Data analysis**

Analyses will be performed using SPSS 16.0 (SPSS 16, SPSS Inc., Chicago, IL, USA). Paired-sample t-tests will be used to compare the effects of an 8-week intervention of exercise and diet on different variables. Pearson’s correlation will be calculated to determine associations. The descriptive analyses will calculate the mean and standard deviations for continuous and percentages for categorical variables. A P-value < 0.05 will be used to indicate statistical significance.

•

•

•

•

1. **References**

Brook, R.D. (2006). Obesity, weight loss, and vascular function. *Endocrine* 29(1)**,** 21-25. doi: 10.1385/ENDO:29:1:121.

Collaboration, N.C.D.R.F. (2016). Trends in adult body-mass index in 200 countries from 1975 to 2014: a pooled analysis of 1698 population-based measurement studies with 19.2 million participants. *Lancet* 387(10026)**,** 1377-1396. doi: 10.1016/S0140-6736(16)30054-X.

Korkmaz, H., and Onalan, O. (2008). Evaluation of endothelial dysfunction: flow-mediated dilation. *Endothelium* 15(4)**,** 157-163. doi: 10.1080/10623320802228872.

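### An uncontrolled before-after change, with follow-up tied to completing the programme, cannot carry the objective's claims about effects and mechanisms

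*Protocol*

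**What the plan says.** The Objective reads, in part, "To investigate the effects of an 8-week intervention program of a combination of exercise and diet on cardiovascular function", and it ends by adding the underlying mechanisms to what is to be investigated.

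The Participants section describes a single source of subjects, "Obese adults from a traditional weight loss camp will be recruited to this study", and fixes the two measurement times: "The measurements will be conducted before and after the subjects completed this 8-week weight loss program of exercise and diet". No control group, allocation or untreated observation period is described anywhere in the protocol.

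The Exclusion criteria include "surgery during the intervention period", alongside conditions that can be established at screening.

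On the outcome: "Primary outcome is endothelial function which is assessed by FMD". The Data analysis section then says: "Paired-sample t-tests will be used to compare the effects of an 8-week intervention of exercise and diet on different variables". Pearson correlation is the only other inferential method named, and it is given for associations.

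Only the protocol was available for this point; any separate analysis plan was not seen.

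**The concern.** There are two distinct problems.

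**Attribution.** A paired t-test asks whether the mean change is zero. In one group without a comparator, that change is the sum of the programme's effect and anything else that moved FMD over eight weeks: time, regression to the mean, familiarity with the test, the closed setting, or drift in measurement. The test cannot divide the sum. Correlating the changes in two variables in the same subjects shows that they moved together. It does not show that one is the mechanism of the other.

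**Selection.** The second measurement is tied to having completed the programme, and a paired test uses only subjects with both values. The programme is demanding, with five hours of training on six days a week, so loss related to tolerance or response is credible. In addition, an event that can occur after baseline is written as an exclusion criterion. Followed as written, the plan can decide who counts by what happened during follow-up.

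At stake is the reading of the primary result: a significant change in FMD would be reported as an effect of exercise plus diet, possibly in a selected subset of those who entered.

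**Working it through.** **1. The protocol's own sample size.** The Sample size section gives: "Sample size is calculated based on 1% change in FMD after weight loss with an expected standard deviation in FMD from our laboratory of 1.3" (in per cent), two-sided alpha 0.05, beta 0.20 and a 20% allowance for refusals, total 20. Take 1.3 as the SD of the within-subject change, which the protocol does not say explicitly. The paired t-test then has noncentrality (1.0/1.3) × √n on n − 1 degrees of freedom:

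- n = 15: power 0.791
- n = 16: power 0.820
- 16 / (1 − 0.20) = 20

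The stated 20 reproduces exactly. The arithmetic is not at fault. It confirms that the study was sized for a one-group before-after test with 16 evaluable subjects, so it can meet its power target with four subjects missing.

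**2. What the test can detect without a comparator.** Write the mean change as programme effect + background shift b. Set the programme effect to zero, keep SD 1.3 and n = 16, so the noncentrality is b × √16 / 1.3 = 3.08 × b. The values of b are assumptions, because the protocol gives none.

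| Assumed background shift b (FMD points) | Noncentrality | Chance of a significant result |
|---|---|---|
| 0 | 0 | 5% |
| 0.25 | 0.77 | 11% |
| 0.5 | 1.54 | 30% |
| 1.0 | 3.08 | 82% |

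A shift in the other direction would mask a real effect. So the lack of a comparator limits interpretation both ways.

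**3. Selection on completion.** Assume 16 of 20 have a post value with mean change 1.0, and the remaining 4 would have changed by x. The mean over all enrolled is 0.8 × 1.0 + 0.2 × x, and the completer mean differs from it by 0.2 × (1 − x).

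| Assumed x | All-enrolled mean | Completer mean minus all-enrolled mean |
|---|---|---|
| 0 | 0.8 | +0.2 |
| 0.5 | 0.9 | +0.1 |
| 1.0 | 1.0 | 0 |
| 1.5 | 1.1 | −0.1 |

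The sign turns on whether x is below or above the completers' mean. Nothing in the protocol fixes x, or the number who would be missing.

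**4. The surgery criterion.** The other items in the list are conditions or histories that can be checked at entry. This one names a period that begins after baseline. Unplanned surgery in that period cannot be known at screening, so taken literally the criterion removes subjects on follow-up information. The protocol gives no figure from which its effect could be computed.

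**The case against.** The other side has several fair points.

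- The single-group design is open and deliberate, and the sample size matches it. The objective concerns the combination of exercise and diet, so failing to separate the two is no defect. This stands. What remains is the failure to separate the package from time, setting and measurement.
- The Data analysis section uses correlation only for associations and makes no mechanistic claim itself. True, but the Objective does make one, and no other analysis is named to serve it.
- The sentence on measurement times may simply describe timing. No rule says that non-completers are dropped, and handling of missing values may sit in an analysis plan. It stands that a completers-only analysis is an inference. However, an analysis plan can only model missing values; it cannot supply measurements that the protocol did not schedule.
- The 20% is an allowance for refusals, which may mean people who decline to take part rather than people who leave. Campers cannot come and go freely, which may also limit early departure. Both points stand, so 4 missing of 20 is an illustration and not the plan's forecast.
- The surgery item may have been meant as surgery already planned at entry, and its effect in 20 subjects is probably small. Also fair, but the text does not say planned.

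A reader might infer that the reported effect is inflated, for instance by 25% (1.0/0.8) if leavers do not change, or by 11% (1.0/0.9) if they change by half a point. The document does not support that. Those figures come from choosing only values of x below 1.0; at 1.0 the bias vanishes and at 1.5 it reverses.

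**Conclusion.** The point holds in a limited form. One uncontrolled group, measured before and after completing the programme and analysed by paired t-test and correlation, can show a within-group change and associations. It cannot by itself support the causal and mechanistic reading that the Objective invites. This conclusion needs no assumed figures.

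The estimate may also be biased by selection on completion or on events after baseline. Upward bias is plausible if those who leave benefit less, but direction and size cannot be derived from the protocol. The illustrative all-enrolled means of 0.8 to 1.1 against a completer mean of 1.0 rest on assumed values for the number missing and for their change. The surgery wording is a smaller matter of clarity. The sample-size calculation is not in question here, provided that 1.3 is the SD of the change.

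**What to change.** 1. **Objective.** Restate the objective and the permitted conclusion as within-group change from before to after the programme. Describe correlations as exploratory associations and not as evidence of mechanism.
2. **Participants and Data analysis.** Schedule the week-8 measurement for every subject with a baseline, whether or not the programme was completed, and include all available values in the primary analysis. Report the number and baseline FMD of those without a post value. Add a sensitivity analysis over a range of assumed changes for them, on both sides of the observed mean. Three substitutes would not do this cleanly: a mixed model with two time points gains little from baseline-only subjects, a single zero imputation is arbitrary, and a departure-day measurement mixes lengths of exposure.
3. **Exclusion criteria.** Reword the surgery item as surgery already planned at screening. Keep subjects who have unplanned surgery in the analysis, flagged.

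The cost is a few extra measurement slots, some wording, and a more modest claim. The second change should be made before enrolment, because missed week-8 values cannot be recovered.

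If the sponsor wishes to keep a causal objective, rewording is not enough and a concurrent control would be needed. With a between-group difference in change of 1.0, SD of change 1.3 in both arms, 80% power and two-sided 0.05, that is 28 evaluable per arm, or 28/0.8 = 35 enrolled per arm, 70 in all.

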**Inclusion criteria**

Obese adults (aged 18 years and over) have a body mass index (BMI) ≥ 30 kg/m^2^.

**Exclusion criteria**

Unstable angina pectoris, myocardial infarction within the last 12 months, decompensated heart failure, cardiomyopathy, severe valvular heart disease, considerable pulmonary disease, uncontrolled hypertension, kidney failure, orthopaedic and/or neurological limitations to exercise, surgery during the intervention period, and drug or alcohol abuse.

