**Resting heart rate and brachial blood pressure**

Resting heart rate (HR) and brachial systolic / diastolic blood pressure (SBP / DBP) will be measured in triplicate using a sphygmomanometer while the subjects are seated for at least 10 min, and the average of the three readings will be recorded.

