**Endothelial function**

Endothelial function will be assessed by brachial artery FMD using echography (UNEX-EF, UNEX Co. Ltd., Nagoya, Japan). The subjects will rest in the supine position for 30 min in a quiet air-conditioned room, and then the right brachial artery will be scanned in longitudinal sections 2-10 cm above the elbow. A pneumatic cuff will be placed around the forearm and will be inflated for 5 min to at least 50 mmHg above systolic pressure. The brachial artery will be scanned and its baseline diameter will be recorded before cuff inflation, and then continuously from the release point to 2 min after cuff deflation to obtain the maximum diameter during reactive hyperemia. FMD is calculated as the maximum percent increase in arterial diameter during continuous measurement of arterial diameter following cuff deflation. Subsequently, endothelium-independent dilation will be measured by administrating 500 µg of nitroglycerine (NTG) sublingually.

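### Every subject is given sublingual nitroglycerine for a study measurement, but nothing in the protocol screens for nitrate contraindications or pregnancy

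*Protocol*

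**What the plan says.** *Who can enter.* The Protocol's *Inclusion criteria* are a single sentence, "Obese adults (aged 18 years and over) have a body mass index (BMI", with the cut-off set at 30 kg/m². There is no upper age limit and no condition on sex or childbearing status.

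*Who is kept out.* The *Exclusion criteria* are also one sentence: "Unstable angina pectoris, myocardial infarction within the last 12 months, decompensated heart failure, cardiomyopathy, severe valvular heart disease, considerable pulmonary disease, uncontrolled hypertension", then "kidney failure, orthopaedic and/or neurological limitations to exercise, surgery during the intervention period, and drug or alcohol abuse". No phrase marks the list as illustrative, and no clause lets the investigator exclude others at discretion.

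*What is given.* Under *Endothelial function*, after the flow-mediated dilation (FMD) scan, "endothelium-independent dilation will be measured by administrating 500 µg of nitroglycerine (NTG) sublingually". The section speaks of the subjects in general and names no subgroup, pre-dose question, blood pressure limit or observation after the dose.

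*When.* Under *Participants*: "The measurements will be conducted before and after the subjects completed this 8-week weight loss program of exercise and diet".

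*What it is for.* "Primary outcome is endothelial function which is assessed by FMD". The secondary outcomes named in the same section do not mention endothelium-independent dilation or nitroglycerine.

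**The concern.** The diet and training belong to the camp that these adults attend. Nitroglycerine does not: it appears in neither the diet nor the exercise section, only as a measurement step. It is reasonable to infer that the study alone is the reason for giving it. Eligibility and dosing safeguards for such a drug belong in the protocol, and an analysis plan would not be expected to supply them.

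What is at stake is participant safety. Someone taking an interacting drug, known to be hypersensitive to nitrates, with low resting blood pressure, or pregnant meets the criteria as written. The measurement section then directs that this person be dosed.

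**Working it through.** No figure in the protocol bears on this point, so the check sets the sections side by side.

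**Step 1. Is the dose restricted anywhere?** No. Neither *Endothelial function* nor any other section shown limits it to a subset or states when to withhold it.

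**Step 2. Does any stated criterion or procedure cover each item?**

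| Item | Nearest text in the Protocol | Does it cover the item? |
|---|---|---|
| Interacting medication | Drug or alcohol abuse (*Exclusion criteria*) | No: abuse is not prescribed medication |
| Nitrate hypersensitivity | None | No |
| Low resting blood pressure | Uncontrolled hypertension (*Exclusion criteria*); the blood pressure section | No: the first concerns high pressure, the second is a recording only |
| Pregnancy | None | No |

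**Step 3. Does the blood pressure reading act as a safeguard?** Pressure "will be measured in triplicate using a sphygmomanometer while the subjects are seated for at least 10 min" and the three readings are averaged. No value is tied to a decision, and the protocol does not say that the reading comes before the nitroglycerine. The data for a safeguard exist, but the instruction to use them does not.

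**Step 4. Do consent and ethics review fill the gap?** The protocol says "Informed consent will be obtained from each individual prior to the measurements" and that ethics approval will be obtained. Neither statement tells the staff member holding the tablet or spray whom not to dose. The consent pages are not in the text reviewed, so they may contain a warning.

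**Step 5. What would be lost by omitting the step for an affected subject?** FMD is recorded first and nitroglycerine follows. Endothelium-independent dilation is not a named outcome. So no named outcome is lost.

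**Step 6. Does the sample size enter?** No. The stated 20 subjects can be reproduced by taking the 1.3% standard deviation as that of the within-subject change: a paired t-test for a 1% change, two-sided α = 0.05 and 80% power needs n = 16 (power 0.82), and 16 / (1 − 0.20) = 20. Nothing here alters that figure.

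**The case against.** **The fault rests on knowledge from outside the protocol.** The documents do not say that these items matter for nitroglycerine. That is true and is stated here as an assumption. That nitrates have contraindications is ordinary clinical knowledge, not a recollection of a particular source, and the fix refers to the product labelling for the exact list.

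**It is an omission, not a contradiction.** The two sections do not conflict. But the criteria are given in full and the dose is fixed without exception. Together they permit dosing someone who should not be dosed, which goes beyond missing detail.

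**The setting and the cardiac exclusions lower the risk.** Subjects have rested supine for 30 minutes before the scan, a single dose is given, and several serious cardiac conditions are excluded. This stands and tempers the concern. It does not cover any of the four items in the table.

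**Some of the text is not shown.** Consent pages were removed, so a safeguard there cannot be ruled out. This stands too.

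Four stronger readings may tempt a reader, and the documents do not support them:

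- *That the count of doses measures the risk.* With dosing at both visits, 20 subjects give 20 × 2 = 40 doses. If 20% leave after baseline, the count is 20 + 16 = 36; if 20% decline before any measurement, 16 × 2 = 32. The protocol speaks of refusal and does not say which applies. In any case these are exposures, not people at risk.
- *That breastfeeding should exclude a woman from the whole study.* No reason for this appears in the documents. If the labelling advises against the drug, skipping that step is enough.
- *That pregnancy would bias the results.* It could change weight, body composition and blood pressure in an uncontrolled before-after comparison, but nothing in the documents gives a frequency or size.
- *That the nitroglycerine measurement has no purpose.* It sits under *Endothelial function*, and the secondary outcomes are introduced as including the listed items. One can say only that it is not named.

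**Conclusion.** The point holds as a participant-safety gap. Nitroglycerine is given to all subjects as a study measurement, and neither the eligibility criteria nor the measurement section screens for interacting medication, nitrate hypersensitivity, low resting blood pressure or pregnancy.

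Its size cannot be given: the number of subjects affected is unknown and may be zero. The conclusion rests on three things: the general pharmacology of nitrates; reading the eligibility lists as complete, since nothing in them suggests otherwise; and the absence of any safeguard in the text available, with consent pages unseen.

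A reader might infer that the primary result is compromised. It is not: FMD is measured before the dose, and no effect on FMD, the primary analysis or the sample size is claimed. The change is worth making because it is cheap and protects participants.

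**What to change.** 1. Add *pregnancy* to the *Exclusion criteria*. This is warranted apart from the drug, because the programme restricts intake to 1300–2200 kcal a day and includes five hours of daily training.

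2. Add to *Endothelial function*: *Before each dose, subjects are checked against the contraindications and interacting drugs in the nitroglycerine product labelling, and the resting blood pressure already measured is reviewed for hypotension; for those affected, including breastfeeding subjects if the labelling advises, only the nitroglycerine step is omitted.* The blood pressure reading must then be scheduled before the dose.

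The cost is one word in the criteria, one sentence in the procedure and a few questions at each dosing. A few nitroglycerine readings will be missing and a few campers may become ineligible. Subjects who skip only this step still contribute FMD and every named secondary outcome.
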